## Abstract

**Background:**

Smoking is the largest preventable cause of morbidity and mortality in Brazil. Education Against Tobacco (EAT) is a large network of medical students in 13 countries who volunteer for school-based prevention in the classroom setting. A recent quasi-experimental EAT study conducted in Germany showed significant short-term smoking cessation effects on 11- to 15-year-old adolescents.

**Objective:**

The aim of this study is both to describe and to provide the first randomized long-term evaluation of the EAT intervention involving a photoaging app for its effectiveness to reduce the smoking prevalence among 12- to 17-year-old pupils in Brazilian public schools.

**Methods:**

A randomized controlled trial will be conducted among approximately 1500 adolescents aged 12 to 17 years in grades 7-11 of public secondary schools in Brazil. The prospective experimental study design includes measurements at baseline and at 6 and 12 months postintervention. The study groups will consist of randomized classes receiving the standardized EAT intervention (90 minutes of mentoring in a classroom setting) and control classes within the same schools (no intervention). The questionnaire measures smoking status, gender, social, and cultural aspects as well as predictors of smoking. Biochemical validation of smoking status is conducted via random carbon monoxide measurements. The primary end point is the difference of the change in smoking prevalence in the intervention group versus the difference in the control group at 12 months of follow-up. The differences in smoking behavior (smoking onset, quitting) between the 2 groups as well as effects on the different genders will be studied as secondary outcomes.

**Results:**

The recruitment of schools, participating adolescents, and medical students was conducted from August 2016 until January 2017. The planned period of data collection is February 2017 until June 2018. Data analysis will follow in July 2018 and data presentation/publication will follow shortly thereafter.

**Conclusions:**

This is the first evaluative study of a medical student–delivered tobacco prevention program in Brazil and the first randomized trial on the long-term effectiveness of a school-based medical student–delivered tobacco prevention program in general.

**ClinicalTrial:**

ClinicalTrials.gov NCT02725021; https://clinicaltrials.gov/ct2/show/NCT02725021 (archived by WebCite at http://www.webcitation.org/6njy3nNml)

## Introduction

Smoking is one of the main risk factors both for mortality and disability-adjusted life years (DALYs) for noncommunicable chronic diseases in Brazil and globally [1-3]. A study published in 2011 estimated the tobacco-related burden in Brazil and found that smoking was accountable in that year for 147,072 deaths and 2.69 million DALYs, representing a direct cost for the health system of $23.37 billion Brazilian real (US $7.37 billion) [4].

According to a large national study that was conducted in 2012 with 61,037 9th graders in Brazil, over 30.0% of 13- to 15-year-olds try smoking before the age of 12 (National School Health Survey—PeNSE) [5]. The newest data from the 2016 ERICA study with 74,589 Brazilian 12- to 17-year-old participants revealed a current smoking prevalence of 5.7% in this young age group with more smokers in public than in private schools (5.9% vs 4.4%) [6]. Although smoking rates among adolescents and emerging adults have substantially declined since the early 2000s, prevalence is still high and strong socioeconomic and educational inequalities in smoking exist in Brazil [6].

Founded in 2012 in Germany, Education Against Tobacco (EAT) has now enrolled participants in over 80 medical schools in 13 countries worldwide. The network has its roots in the school-based interventions delivered by medical students that cost about US $20 per participating class and reach up to 40,000 students per year worldwide. However, the network is also involved in medical education research on smoking cessation counseling, science-based multilanguage apps, and public awareness and advocacy for tobacco control [7-9].

The school-based intervention has only been evaluated for short-term effects with a quasi-experimental design with multiple potential sources of bias [10,11]. However, its preliminary evaluation involving 1474 students showed a significant reduction in the smoking prevalence of secondary school students in Germany at 6 months of follow-up after interventions motivating them to quit [10,11]. After this first evaluation, the curriculum was optimized for students with a lower educational level because the intervention was less effective in this subgroup [11]. This was done by making the program more interactive and by developing and involving a photoaging app (Smokerface) into our classroom intervention because published research suggests that there is effectiveness of photoaging strategies for our age group [7].

The European Smoking Prevention Framework Approach (ESFA) program developed and tested a smoking prevention program for adolescents aged between 12 and 15 years (students enrolled in the 7th-9th school grades) in 6 European countries [12]. Studies on the ESFA project have shown mixed outcomes: only Portugal, Spain, and Finland achieved positive results [13]. We suspect there will be differences between the outcomes in Brazil and the ones we found in Germany.

Smoking is largely conceptualized to medical students as an adult health problem, although most long-term smokers started as adolescents. Recent studies indicate that tobacco addiction is substantially undertreated by physicians in comparison with other chronic conditions such as diabetes or hypertension [14-16]. The authors conclude that this is mainly due to lack of motivation, skills, and knowledge from the medical community [14-16]. There is evidence that medical student training addressing adolescent health promotion to prevent smoking can increase the frequency of obtaining smoking status of and providing advice to patients [17]. The importance of primary and secondary prevention of smoking uptake has led to calls for a greater engagement and training of future physicians in tobacco control [14]. In this context, the EAT network not only provides school-based prevention but also sensitizes future physicians to the importance of tobacco prevention and cessation [10,11,18].

The aim of this publication is both to describe the optimized EAT intervention and to present the study protocol of a trial designed to determine the long-term effectiveness of the school-based EAT intervention in reducing the smoking prevalence among secondary school students in Brazil.

## Methods

### Ethics Approval and Consent to Participate

In accordance with Good Epidemiologic Practice guidelines [19], the study protocol was submitted for approval by the responsible ethics committee (Federal University of Ouro Preto, Brazil), and consent was obtained. All legal and data protection issues were discussed with the responsible authorities, and all participants are required to provide active informed consent.

### The Education Against Tobacco Intervention

#### Overview

The school-based intervention under evaluation consists of a 90-minute module in the classroom setting. It is presented by 2 medical students per classroom to about 25 pupils at a time discussing features of smoking that students can relate to in their everyday life in a gain-framed and interactive manner. The goal is to initiate and guide the student evaluation process of smoking with age-appropriate information that helps them to reframe a positive nonsmoking image by asking for their opinions and views in small group settings. The students form 4 groups (mostly with their friends) and rotate to 4 different stations in the classroom.

#### Station 1

This station, built up near a window or outside, discusses different tobacco products and extraction of substances of tobacco smoke. In the first part, different products (including e-cigarettes, a water pipe, and cigarettes) are displayed and their functionality and harmfulness are discussed in a gain-framed manner.

Second, the students are instructed to conduct an experiment using a hand-vacuumizer, a napkin, a plastic bottle and a cigarette. The napkin is put between cigarette and bottle and burned down to demonstrate the ingredients of the smoke by the discoloration of the napkin. The process is repeated with e-cigarettes that show little discoloration and are regarded as less harmful but still contain cancerogenic substances [20].

#### Station 2

The attractiveness and photoaging consequences of nonsmoking and mechanisms related to the face are discussed. In the first part, pictures of monozygotic non-/smoking twins are displayed that were extracted from the publication of Okada et al [21]. The students are asked which twin is the smoker and what differences they note.

In the second part, Galaxy Tab E tablets (Samsung Electronics Inc, Seoul, Korea) are used to show each student the effects of non-/smoking on their own faces by the help of the photoaging app Smokerface that we described and piloted in great detail elsewhere [7,9]. By this means, the students’ faces are captured via a selfie and photoaged into 1- and 15-years-older versions of themselves (normal aging vs normal aging plus smoking) (Figures 1 and 2 and Multimedia Appendix 1 demonstrate the effects of the app). The app’s underlying aging algorithms are based on publications showing an increased risk for acne, pale skin, wrinkles, and other capillary and connective tissue changes in smokers. The use of the app influences numerous predictors of smoking in students of this age group in accordance with the theory of planned behavior and as demonstrated in our recent paper [9].

**Figure 1 figure1:**
[figure not shown]
Photoaged image of a 17-year-old woman showing the consequences of smoking 1 pack a day for 1 year (vs nonsmoking).

**Figure 2 figure2:**
[figure not shown]
Photoaged image of a 17-year-old woman showing the consequences of smoking 1 pack a day for 15 years (vs nonsmoking).

#### Station 3

Performance benefits of nonsmoking (physical performance, stress, common colds) and understanding the mechanisms of how tobacco smoking affects the body with age-appropriate examples (eg, occluded vessels lead to loss of connective tissue in women’s breasts which equals less volume and tightness and impotence in both men and women [22], pale skin, mechanisms of acne); this is explained via pencil-and-paper drafts and interactive questions. In addition, obesity [23,24], lung growth [25], and body growth impairment in adolescent smokers are discussed on a body model with pencil-and-paper sketches and by the use of growth curves [24].

#### Station 4

The aim of this station is to discuss the student’s own experiences with tobacco and how they reacted in the past to peer pressure and to the strategies of the tobacco industry to influence their decision. The groups’ knowledge and experience is shared and discussed in a team setting where the medical students take the role of older friends by complementing the students’ experiences with their own experiences to increase the perceived self-efficacy of the students, which is the most important predictor of future smoking in accordance to the theory of planned behavior [26]. It has been shown to predict both the intention to smoke and actual smoking behavior in a meta-analysis [27].

At the end of the classroom seminar we ask for the students' final judgments on smoking to create positive peer pressure and influence the students’ subjective norm in accordance with the theory of planned behavior [26]. As a final exercise, all students breathe through a straw after having physically exercised in the classroom together to learn how lung impairment due to smoking feels with exercising.

Overall, long-term health consequences are not discussed in great detail as fear approaches were proven to be ineffective and information on the diseases can be found on every cigarette pack [28]; besides that, these long-term harms (such as lung cancer, vascular disease, and chronic pulmonary disease) are too far in the future to fathom. Instead, the program focuses on information relevant for teenagers, particularly related to attractiveness and physical performance, as both of these aspects have been shown in several publications to strongly influence the behavior, self-confidence, and quality of life of adolescents [29-31].

### Design

A randomized controlled trial will be conducted among approximately 1500 adolescents in grades 7-11 of secondary schools in Brazil (Figure 3). The planned study period is February 2017 until June 2018. The prospective experimental study design includes measurements at baseline (t1) and 6 months (t2) and 12 months (t3) postintervention. The study groups will consist of randomized classes receiving the standardized EAT intervention (90 minutes of mentoring in a classroom setting) and control classes within the same schools (no intervention). The study questionnaire that measures smoking status and gender, social, and cultural aspects uses items from previously tested and published questionnaires. By the use of the conceptual method for translation described by the World Health Organization/United Nations Economic and Social Commission for Asia and the Pacific Project on Health and Disability Statistics, the items were translated to Portuguese [32] and afterwards pretested with students from Brazil [32]. Smoking status is validated by a random carbon monoxide (CO) breathing test at baseline and endline.

Baseline collection will be completed by mid-February 2017. The intervention will be conducted from end of February 2017 until May 2017. The first follow-up survey will be 6 months thereafter. At 1-year follow-up (May/June 2018), the data collection is complete.

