### Participants and Sample Size

In accordance with the first evaluation of our program in Germany, a total of 1500 eligible secondary school students will be recruited [7]. Inclusion criteria are the attendance of grades 7-11 at public secondary schools in Brazil with age ranging from 12 to 17 years. Exclusion criteria are defined as inability to fulfill the inclusion criteria (ie, private schools, different grades). The age range for inclusion in the study is higher than in our German study [10] as the median age of smoking onset is higher in Brazil than in Germany [6,11]. As we expect the same loss-to-follow-up effect as in our quasi-experimental trial in Germany (18.6%), a test power of 70% and a 2-sided alpha of .05 are considered appropriate for our primary end point.

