### Biochemical Validation

Using a portable CO analyzer (Smokerlyzer piCO+, Bedfont Scientific Ltd), CO testing will be randomly performed at baseline and endline in at least 10% of students [37]. CO measurements will be supervised by medical students with recordings made in the afternoon. The cutoff point is defined as 6 parts per million or less for nonsmoking and more than 6 parts per million for smoking [38-40].

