### Outcomes

The primary end point is the difference of the change in smoking prevalence in the intervention group versus the difference in the control group at 12 months of follow-up. The same longitudinal prevalence effects are studied on our females exclusively as a secondary outcome because our photoaging intervention is suspected to be more successful in females [41]. As our sample size is quite small, the secondary outcome criteria is met if 20% fewer females start smoking in the intervention group during the study period of 1 year. The differences in smoking behavior (smoking onset, quitting) between the 2 groups will be studied as additional secondary outcomes with a positive 20% difference in change of behavior set as met outcome criteria. A smoker is defined as a pupil who claims to smoke at least once in the past 30 days within the survey.

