### Limitations

Limitations and advantages of the CO testing in exhaled air have been described in great detail elsewhere [37]. Conclusively, our method used for biochemical validation is a widely accepted cost-effective procedure even if it does not have the sensitivity of cotinine saliva testing, which is far more costly [33].

As our research is not conducted multinationally, we can not generalize its results to all cultural backgrounds. However, our intervention involves a photoaging intervention and outward appearance has been described to be the most relevant component of the self-concept in adolescents from multiple cultural backgrounds [48], which increases the international validity of our research.

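### A carbon monoxide reading in a minimum 10% subsample is a weak check of recent smoking and cannot validate the self-reported 30-day smoking status on which the primary end point rests.

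*Protocol article*

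**What the plan says.** The Outcomes section defines the status behind the primary end point by self-report: "A smoker is defined as a pupil who claims to smoke at least once in the past 30 days within the survey". The Design section then states: "Smoking status is validated by a random carbon monoxide (CO) breathing test at baseline and endline". The Methods part of the Abstract and the Data Collection section also describe smoking status as biochemically validated by CO.

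The Biochemical Validation section shows what this consists of: "CO testing will be randomly performed at baseline and endline in at least 10% of students". On timing it says: "CO measurements will be supervised by medical students with recordings made in the afternoon". On interpretation: "The cutoff point is defined as 6 parts per million or less for nonsmoking and more than 6 parts per million for smoking". No section says how long after a cigarette a reading stays above the cut-off, and none relates the reading to the 30-day window.

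The Limitations section says that "our method used for biochemical validation is a widely accepted cost-effective procedure even if it does not have the sensitivity of cotinine saliva testing", and refers the other limits of CO testing to a cited source. It mentions neither the 30-day window nor the size of the tested subsample.

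**The concern.** The test and the definition cover different periods. A pupil who smoked once, two weeks ago, is a smoker by the definition, yet may well read at or below 6 ppm. If that pupil denies smoking, the reading appears to support the denial. If the pupil admits it, the reading appears to contradict a true answer. Agreement or disagreement with CO therefore does not show whether 30-day self-report is correct.

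This matters because the main threat to a self-reported end point here is under-reporting that differs by arm. Control classes receive nothing, so pupils know which group they are in. The intervention session closes by asking pupils for their verdict on smoking, with the declared aim of shifting the group norm. Class teachers supervise the questionnaires. Greater reluctance to admit smoking in intervention classes is plausible and would look like a treatment effect. CO testing is the only objective check described, so what it can and cannot exclude decides how the primary result may be presented.

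**Working it through.** The plan gives no figure for the accuracy or precision of the CO check, so there is nothing to reproduce. The calculation uses the plan's design inputs and a range of assumptions.

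**Inputs from the protocol article**
- 1500 pupils and 18.6% loss to follow-up (Participants and Sample Size)
- 1:1 allocation by class (Randomization)
- 5.9% current smoking in public schools (Introduction)
- at least 10% of pupils tested (Biochemical Validation)

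**Assumptions**
- CO sensitivity *s* for a 30-day smoker: 10% to 80%
- share *u* of smokers who deny smoking: 25% or 50%
- no false-positive readings
- pupils treated as independent (clustering by class would widen the bounds)

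**Step 1. Numbers tested at 12 months, at the 10% minimum**
- Completers: 1500 × (1 − 0.186) = 1221, about 610 per arm
- Tested: 1221 × 0.10 = 122.1
- True smokers among them: 122.1 × 0.059 = 7.2 in both arms together
- Nonsmokers: (122.1 − 7.2) / 2 = 57.4 per arm

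At baseline, 1500 × 0.10 = 150 are tested, with 150 × 0.059 = 8.9 true smokers.

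**Step 2. What a clean result excludes, with a perfect test**

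If none of *n* self-declared nonsmokers is CO-positive, the one-sided 95% upper bound on the hidden-smoker share is 1 − 0.05^(1/n).
- 10% tested, n = 57.4 per arm: 5.1%
- 20% tested, n = 114.9 per arm: 2.6%

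The first bound is close to the whole 5.9% prevalence.

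**Step 3. Chance of finding no denier at 12 months with an imperfect test**

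P(none) = (1 − 0.059 × u × s)^122.

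| Sensitivity *s* | 25% deny | 50% deny |
|---|---|---|
| 10% | 84% | 70% |
| 30% | 58% | 34% |
| 50% | 41% | 16% |
| 80% | 24% | 5% |

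**Step 4. The opposite discordance**

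If nobody denies, the honest smokers who read CO-negative number 7.2 × (1 − s): 6.5 at 10% sensitivity, 3.6 at 50% and 1.4 at 80%.

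**Step 5. Overall agreement says little**

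The discordant share is 0.059 × [u·s + (1 − u)(1 − s)], which is never above 0.059. Overall agreement is thus at least 94.1%, even if every smoker denies and the test is perfect.

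**Step 6. How few deniers would matter**

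The primary end point has no stated effect size, so the 20% difference used for the secondary outcomes serves as an illustration. With 610 × 0.059 = 36 smokers per arm, 20% is about 7 pupils. If 7 intervention pupils deny smoking, the chance that the check finds none of them is (1 − 0.10 × s)^7:
- perfect test: 0.90^7 = 48%
- 30% sensitivity: 0.97^7 = 81%

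If 20% are tested with a perfect test, it is 0.80^7 = 21%.

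**The case against.** Much can be said for the plan. It openly defines a smoker by what the pupil reports, gives CO no role in the primary analysis, and concedes that CO is less sensitive than cotinine. Questionnaires are sealed after completion and opened only at the university, which also encourages honest answers. The 10% is a floor, and testing more pupils would narrow the bounds. The article is condensed and the questionnaire is not shown, so an item on last smoking, or a warning that anyone may be tested, may already exist. All of this stands, and it limits the point to what the validation statement can support.

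Three stronger readings are tempting, and the documents do not support them:
- **The test detects only same-day smoking.** No detection window is given, so this can only be an assumption. The working uses a range of sensitivities instead.
- **The check is bound to make false self-report look confirmed.** With high sensitivity and much denial, some deniers would be found (Step 3). With low sensitivity, honest light smokers would look discordant (Step 4). The result could mislead in either direction.
- **The trial will present low discordance as proof of its primary result, or self-report is in fact biased.** The plan says neither. The risk is that bias could not be excluded.

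The objection does not rescue the statement itself. The concession in Limitations concerns sensitivity relative to cotinine. It covers neither the 30-day window nor the number of pupils tested, and the Step 2 bound holds even for a perfect test.

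**Conclusion.** The point holds in limited form. The plan claims validation of smoking status, while the procedure it describes is a spot check of recent smoking in a subsample. At the stated minimum, about 7 true smokers are tested at 12 months across both arms, and a completely clean result would still be compatible with about 5% hidden smokers among self-declared nonsmokers in either arm. Doubling the sample to 20% reduces this to about 2.6%, still a large fraction of a 5.9% prevalence. These figures rest on the plan's own prevalence, loss and sampling floor, on independence between pupils, and on perfect detection, which favours the plan. With imperfect detection the check is weaker by an amount that depends on an unknown sensitivity.

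The trial can proceed as designed, with its sample size and primary analysis unaffected by this point. What should change is how the CO data are compared and reported, and the claim that the primary outcome is biochemically validated.

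**What to change.** 1. Unless the questionnaire already has one, add an item at t1 and t3 on time since last smoking (for example today, yesterday, past 7 days, past 30 days, earlier).
2. Compare CO with same-day or previous-day smoking rather than with 30-day status.
3. Report both directions of discordance (deniers who read positive, admitted recent smokers who read negative) by arm, with confidence intervals, rather than one overall agreement figure.
4. If this is not already done, tell pupils in both arms, before they fill in the questionnaire, that anyone may be selected for a breath test.
5. Reword the Abstract, Design and Data Collection sections to say that recent smoking is checked in a random subsample and that the 30-day end point rests on self-report. Add the time-window mismatch and the subsample size to Limitations.

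The cost is one questionnaire item, one scripted sentence at each survey and a small added table. No further breath tests are needed. The real price is that the primary outcome can no longer be described as biochemically validated. Testing more than the 10% minimum would tighten the bounds, but is not required for these changes.
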